### Concomitant care permitted or prohibited during the trial {15d}

During the trial, participants will be permitted to continue their standard pharmacological treatments for CRC, including chemotherapy (e.g., FOLFOX), as prescribed by their oncologist. Routine medical care, including visits to the oncology clinic, will also be maintained according to the standard practice of the participating hospitals. Pain relief medications and other supportive treatments, such as antiemetics or antidiarrheals, will be allowed if necessary for managing chemotherapy-related symptoms.

To maintain the integrity of the study, the use of dietary supplements (including fish oil, omega-3 fatty acids, multivitamins, calcium, vitamin D, or herbal supplements) outside of the study interventions will be prohibited. The use of probiotics will also be restricted to avoid potential confounding effects on gut microbiota and gastrointestinal symptoms. Furthermore, participants will not be permitted to follow any other dietary interventions, such as weight loss programmes or therapeutic diets, unless recommended by their treating physician for medical reasons. The use of NSAIDs and immunosuppressive medications will be restricted, except for cases where these are prescribed for managing medical conditions unrelated to the study. Any changes in concomitant care, including medication use, will be documented in the participant’s case report form to ensure the accuracy of the study outcomes.

### Ancillary and post-trial care {34}

Participants will continue to receive all routine clinical care for CRC, including standard supportive management of treatment-related symptoms, throughout the trial, and any medical issues arising during participation will be managed or referred according to usual practice at the participating hospitals. After the final follow-up assessment, participants will return to routine care under their treating oncology team, with ongoing nutritional advice and supportive care provided as clinically indicated. Any trial-related harm will be managed promptly through the established clinical and administrative pathways of the participating hospitals, including the procedures in place for addressing research-related injury and compensation.

### Outcomes {16}

#### Primary outcomes

Grades of CIGT: CIGT will be assessed using the National Cancer Institute Common Terminology Criteria for Adverse Events (CTCAE) v5.0 [18]. Prespecified gastrointestinal toxicities include nausea, vomiting, anorexia, oral mucositis, and diarrhoea. Assessments will be conducted at baseline (T0), day 3 post-chemotherapy (T1), week 1 (T2), week 3 (T4), and week 5 (T6). The confirmatory clinical endpoint is the participant-level incidence of experiencing any prespecified CTCAE gastrointestinal toxicity of grade ≥ 2 during follow-up. Longitudinal CTCAE grades, time-specific binary indicators (grade ≥ 2 at each time point), and the maximum CTCAE grade across the prespecified toxicities will be analysed and reported as supportive outcomes (reported as n [%] and median [IQR]).Serum inflammatory biomarkers: Serum biomarkers, including interleukin-6 (IL-6) and C-reactive protein (CRP), will be measured at the following time points: T0 and week 6 post-chemotherapy (T7). Outcomes will be summarised as concentrations at each time point and change from baseline to week 6 [reported as mean ± standard deviation (SD)].Stool-based multi-omics: Stool samples will be collected at T0, T1, T2, T3, and T7 using a standardised kit and stored at − 80 °C until batch processing. Shotgun metagenomic sequencing will be performed to characterise taxonomic composition and metagenome-derived functional profiles [19]. Sequencing reads will undergo prespecified quality control, filtering, and taxonomic/functional profiling using validated pipelines. Untargeted stool metabolomics will be performed in parallel, with pooled quality control (QC) samples, process blanks, and internal standards included and run order randomised. Metabolomics data will be processed using prespecified procedures (peak detection, alignment, QC-based feature filtering, normalisation/transformation, and batch/drift correction), and metabolite annotation will be supported by tandem mass spectrometry (MS/MS) spectral matching against curated libraries. Feature-level and pathway-level analyses will control multiple testing using false discovery rate procedures. Outcomes will be summarised as within-sample diversity, between-sample dissimilarity, and longitudinal changes in the relative abundance/intensity of key taxa, functional features, and metabolite features/pathways (reported as change from T0 at each time point).

#### Secondary outcomes

Dietary assessment: Dietary assessment will be conducted using a semi-quantitative FFQ and diet records (food diaries). The FFQ will capture usual dietary intake over the preceding week, including consumption frequency and portion size, and will be administered at T0 and T7. FFQ data will be used to derive plant-based diet indices [Plant-Based Diet Index (PDI), healthy Plant-Based Diet Index (hPDI), and unhealthy Plant-Based Diet Index (uPDI)] by applying pre-specified scoring to plant- and animal-food groups, adapted to the Chinese Dietary Guidelines and the study intervention targets [17]. Diet records will prospectively document all foods and beverages consumed over three consecutive days at a randomly selected time during the intervention period (T0-T7). Outcomes will be summarised as index scores at each FFQ time point and change from T0 to T7, and as average daily intake estimates from the 3-day records (reported as mean ± SD).Nutrition assessment: Nutritional status will be evaluated using bioelectrical impedance analysis [Bioelectrical Impedance Analysis (BIA)] and routinely collected clinical laboratory tests at prespecified time points. BIA will be performed with the InBody 370 at T0 and T7 by trained study staff using a standardised procedure [20], yielding body weight and body-composition measures (e.g., fat mass, fat-free mass, skeletal muscle mass, and segmental composition in appendicular and trunk compartments). Routine blood tests will be extracted from the hospital laboratory information system at T0, T3, T5, and T7. Prespecified laboratory domains include nutrition-related markers, lipid and glucose profile, liver and renal function indices, immune cell counts, and tumour markers (Table 1). Outcomes will be summarised as values at each time point and as change from T0 (reported as mean ± SD).Fatigue: Fatigue will be assessed using the Chinese version of the Piper Fatigue Scale-12 (PFS-12) [21], a 12-item self-report instrument covering four dimensions (behavioural, affective, sensory, and cognitive). Each item is rated on a 0–10 numeric scale, and the total score is calculated as the mean of all 12 items (range 0–10), with higher scores indicating more severe fatigue. Assessments will be completed at T0, T3, and T7. Outcomes will be summarised as (i) the PFS-12 total score at each time point and (ii) change from T0 at each follow-up (reported as mean ± SD).Anxiety and depression: Anxiety and depression will be assessed using the Hospital Anxiety and Depression Scale (HADS) [22], a 14-item self-report instrument comprising two 7-item subscales (anxiety and depression). Items are rated on a 4-point scale, yielding subscale scores from 0 to 21, with higher scores indicating greater symptom severity. Assessments will be completed at T0, T3, and T7. Outcomes will be summarised as (i) anxiety and depression subscale scores at each time point and (ii) change from T0 at each follow-up (reported as mean ± SD).Physical activity: Physical activity will be assessed using the Chinese short form of the International Physical Activity Questionnaire (IPAQ-C) [23]. The questionnaire captures self-reported walking, moderate-intensity activity, and vigorous-intensity activity over the previous 7 days. Participants will be classified into low, moderate, or high physical activity according to the IPAQ scoring protocol. Assessments will be completed at T0, T3, and T7. Outcomes will be summarised as the proportion of participants in each physical activity category at each time point and the change in category from T0 to each follow-up (reported as n, %).

**Table 1 Tab1:** Routine blood tests

Category	Blood counts
Nutrition-related markers	TP, ALB, Hb, Fe, Mg, Ca
Liver and renal function indices	ALT, AST, Cr, eGFR
Lipid- and glucose-related markers	TC, TG, LDL-C, HDL-C, glucose
Immune-related cell counts	WBC, neutrophil count, TLC
Tumour markers	CEA, CA19-9

*TP* total protein, *ALB* albumin, *Hb* haemoglobin, *Fe* iron, *Mg* magnesium, *Ca* total calcium, *ALT* alanine aminotransferase, *AST* aspartate aminotransferase, *Cr* creatinine, eGFR estimated glomerular filtration rate, *TC* total cholesterol, *TG* triglycerides, *LDL-C* low-density lipoprotein cholesterol, *HDL-C* high-density lipoprotein cholesterol, *WBC* white blood cell count, *TLC* total lymphocyte count, *CEA* carcinoembryonic antigen, *CA19-9* carbohydrate antigen 19–9

### Harms {17}

Potential harms related to the dietary interventions include food allergy/intolerance, hypoglycaemia, clinically relevant weight loss, headache, and other unexpected symptoms during the intervention period. Adverse events will be actively captured at each scheduled contact from T0 to T7, and participants may report events between contacts via telephone or WeChat. All adverse events will be recorded on a prespecified case report form and graded using CTCAE v5.0 [18]. For each event, onset/resolution dates, CTCAE grade, relatedness to the intervention, actions taken, and outcome will be documented. Serious adverse events and events requiring urgent medical attention will be managed according to routine clinical practice and reported to the ethics committee in a timely manner. Safety data will be reviewed by a designated safety monitor, who may recommend modification or discontinuation of the intervention if unacceptable harms are observed. Harms will be summarised by group as incidence and severity distribution, with particular attention to grade ≥ 2 events, serious adverse events, and events leading to discontinuation.

### Participant timeline {18}

T0 is defined as baseline (before initiation of the allocated dietary intervention and within the chemotherapy admission). Follow-up time points are anchored to the start of the chemotherapy cycle: T1, day 3 post-chemotherapy; T2, week 1; T3, week 2; T4, week 3; T5, week 4; T6, week 5; and T7, week 6. There is no run-in or washout period. After eligibility screening and written informed consent, participants will be randomised (1:1:1) to one of three dietary strategies and followed for 6 weeks across inpatient chemotherapy and the home-based interval period. Assessments will be conducted in person during inpatient visits when feasible and otherwise via scheduled telephone/WeChat contacts according to the timetable below. Table 2 shows the participant timeline.

**Table 2 Tab2:**
[figure not shown]
Schedule of enrollment, interventions, and assessments

^†^3-day diet records: The diet record will be completed once at a randomly selected time point during the intervention period (T0-T7)

X indicates discrete time-point activities/assessments

Horizontal arrows indicate procedures delivered continuously over the interval (t0-t7)

### Sample size {19}

Sample size was estimated using the Tests for Two Proportions module in PASS 2025 for the primary endpoint, defined as experiencing any prespecified CTCAE gastrointestinal toxicity of grade ≥ 2. Given two prespecified primary comparisons, a Bonferroni-adjusted two-sided α of 0.025 and 80% power were applied. Based on Souza et al. [24], the assumed proportions were 0.176 in the intervention group and 0.533 in the control group. Under these assumptions, 30 evaluable participants per group are required for each primary comparison. To account for an anticipated 20% loss to follow-up, this was rounded up to 38 participants per arm (total N = 114; 1:1:1).

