### Trial design {12}

The trial is designed with a superiority framework and an allocation ratio of 1:1:1. Participants will be randomised to receive a plant-based dietary intervention, a conventional dietary intervention, or a conventional dietary intervention supplemented with an Oncology Complete Nutritional Formula for a 6-week intervention period. The trial protocol is reported in accordance with the Standard Protocol Items: Recommendations for Interventional Trials (SPIRIT) guidelines [16]. The study flow is illustrated in Fig. 1.

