## Statistical methods

### Statistical methods for primary and secondary outcomes {27a}

Analyses will be prespecified in the statistical analysis plan (SAP) and conducted using R and/or SPSS. Baseline characteristics will be summarized by group using mean ± SD or median (IQR) for continuous variables and n (%) for categorical variables. Two primary comparisons will be performed: plant-based diet versus conventional diet, and plant-based diet versus conventional diet plus oncology nutritional formula. To control the family-wise type I error across the two primary comparisons, we will use a Bonferroni-adjusted two-sided α of 0.025 for each comparison [26]. Within each comparison, the three co-primary outcomes will be tested using a pre-specified hierarchical gatekeeping procedure in the following order: (1) CIGT, (2) serum inflammatory biomarkers, and (3) stool-based multi-omics. For the confirmatory test of the first co-primary outcome (CIGT), the primary clinical endpoint is the participant-level incidence of experiencing any prespecified CTCAE gastrointestinal toxicity of grade ≥ 2. Testing will proceed to the next outcome only if the preceding outcome is statistically significant at the same two-sided α level; otherwise, subsequent outcomes will be analysed and reported as supportive/exploratory without confirmatory claims.

The confirmatory analysis of the primary clinical endpoint will use logistic regression with adjustment for the stratification factors (site and sex) and other prespecified covariates as applicable. Longitudinal continuous outcomes will be analysed using linear mixed-effects models with fixed effects for group, time, and group-by-time interaction and a participant-level random intercept (and random slope if supported), adjusting for the baseline value of the outcome (when applicable) and the stratification factors. Longitudinal ordinal CTCAE grades and time-specific binary indicators (e.g., grade ≥ 2 at each time point) will be analysed as key secondary/supportive outcomes using mixed-effects ordinal logistic models and mixed-effects logistic regression, respectively, with the same covariate structure.

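### The 80% power at 30 per group belongs to an unpooled Z-test, is a few points lower for the planned logistic regression, and rests on an unsupported risk in the formula comparison

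*Protocol article*

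**What the plan says.** Protocol article, Sample size {19}: "Sample size was estimated using the Tests for Two Proportions module in PASS 2025". The design values are that "a Bonferroni-adjusted two-sided α of 0.025 and 80% power were applied" and that "the assumed proportions were 0.176 in the intervention group and 0.533 in the control group", both taken from one cited study. The section concludes that "30 evaluable participants per group are required for each primary comparison", then allows for 20% loss to reach 38 per arm and 114 in total. It does not name the test statistic or the variance form.

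Statistical methods for primary and secondary outcomes {27a} sets out two primary comparisons: "plant-based diet versus conventional diet, and plant-based diet versus conventional diet plus oncology nutritional formula". It also says that the "confirmatory analysis of the primary clinical endpoint will use logistic regression with adjustment for the stratification factors (site and sex"), together with other covariates as applicable. The article does not say whether the treatment effect will be judged by a Wald or a likelihood-ratio test.

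Explanation for the choice of comparator {9b} gives the formula arm its own purpose, which is to separate the effect of the dietary pattern from that of supplementation.

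**The concern.** Two things look wrong.

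First, the test behind the sample size is not the test that will be used. Forms of the two-proportion test that agree in large samples differ visibly at 30 per group, so the 80% may not carry over to the logistic model.

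Second, the claim of adequacy covers each primary comparison but uses a single control risk. It holds for plant-based versus formula only if the formula arm has the same 0.533 risk of grade 2 or worse toxicity. The article does not say this or argue for it. The arm is there because supplementation might have an effect of its own, whereas the calculation gives it none.

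At stake is how far the stated power can be trusted, mainly for the second comparison. Under the gatekeeping in {27a}, failing on gastrointestinal toxicity within a comparison also reduces that comparison's biomarker and stool outcomes to exploratory status.

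**Working it through.** **Inputs (Sample size {19}).** p1 = 0.176, p2 = 0.533, difference 0.357, alpha 0.025 two-sided (z = 2.2414), power 80% (z = 0.8416), loss 20%.

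**1. The plan's own figure.** Unpooled Z formula:

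n = (2.2414 + 0.8416)² × [0.176 × 0.824 + 0.533 × 0.467] / 0.357²
= 9.505 × (0.1450 + 0.2489) / 0.12745 = 29.4, so 30.

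Loss: 30 / 0.80 = 37.5, so 38. Total: 3 × 38 = 114. All three figures reproduce.

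**2. Another common choice.** Pooled Z (chi-square) formula with mean risk 0.3545:

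n = [2.2414 × √(2 × 0.3545 × 0.6455) + 0.8416 × √0.3939]² / 0.12745
= (1.516 + 0.528)² / 0.12745 = 32.8, so 33.

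The arcsine formula gives 32. Of the formulas tried at two-sided 0.025, only the unpooled one gives 30.

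**3. Exact power for 0.176 versus 0.533**, summing over both binomial distributions, without covariates:

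| Test | 30 per group | 38 per group |
|---|---|---|
| Unpooled Z | 0.792 | 0.881 |
| Pooled Z (chi-square) | 0.771 | 0.871 |
| Logistic, likelihood ratio | 0.771 | 0.871 |
| Logistic, Wald | 0.752 | 0.861 |

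The likelihood-ratio test first passes 80% at 32 per group (0.812) and the Wald test at 33 (0.805). The gap is therefore 2 to 3 participants per group.

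**4. The planned adjusted model, by simulation.** Site and sex were included as covariates. An even split of each and the size of their effects are assumptions, since the article gives neither. Marginal risks were held at 0.176 and 0.533. Power at 30 per group:

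| Assumed odds ratio of each covariate | Wald | Likelihood ratio |
|---|---|---|
| 1 (not prognostic) | 74–76% | 77–79% |
| 2 | about 76% | about 80% |
| 3 | 78–80% | 82–83% |

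At 38 per group with non-prognostic covariates, power is about 86% (Wald) and 87% (likelihood ratio).

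**5. Plant-based versus formula.** Exact unadjusted likelihood-ratio power with the plant-based arm held at 0.176. The formula-arm risks below 0.533 are assumed values, not figures from the article:

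| Formula-arm risk | 30 per group | 38 per group |
|---|---|---|
| 0.533 (as in the plan) | 0.77 | 0.87 |
| 0.50 | 0.69 | 0.80 |
| 0.45 | 0.54 | 0.66 |
| 0.40 | 0.38 | 0.49 |

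By the pooled formula, 80% power at risks of 0.50, 0.45 and 0.40 would need 40, 54 and 77 evaluable per group.

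**The case against.** Nothing is miscalculated. Unpooled variance is a legitimate choice in a two-proportions module, and sizing an adjusted logistic analysis with a two-proportion formula is ordinary practice. The article does not claim that its 80% was computed for the logistic model. Adjustment can also recover the shortfall: with moderately or strongly prognostic covariates the likelihood-ratio test reaches 80% or more. Thirty evaluable is the floor after 20% loss, and with all 38 per arm observed every test in step 3 has 0.86 to 0.88 power for the planned contrast. Whether to use Wald or likelihood ratio is a detail that an article may leave to its SAP. All of this stands, and it makes the test mismatch a small matter.

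A reader might go further and infer that the sample size is wrong, or that the logistic analysis is underpowered and N must rise. The documents do not support that. The figures reproduce, and the shortfall is a few points that depend on the test and on covariate effects the article does not state.

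A reader might also infer that a null result against formula will be presented as evidence of no difference. The article says that "The trial is designed with a superiority framework and an allocation ratio of 1:1:1" and nowhere proposes to read a null result as equivalence.

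On the formula arm, the cited study is not at hand, so it cannot be checked which control its 0.533 describes. The formula-arm risk could also be higher than 0.533, since the intervention description {15a} anticipates intolerance such as nausea and diarrhoea. What remains is that the article applies 0.533 to that arm without stating a reason.

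**Conclusion.** The point holds in two parts of unequal weight.

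The lesser part is the stated 80%. At 30 evaluable it is roughly 1 to 6 points above what the planned adjusted logistic regression gives when site and sex carry little prognostic information: 77–79% with the likelihood-ratio test, 74–76% with Wald. The gap closes only under the assumption of prognostic covariates, with odds ratios of about 2 for the likelihood-ratio test and about 3 for Wald.

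The weightier part is the formula comparison. The claim that 30 per group suffices for each comparison has no stated basis there, and power is sensitive to the missing assumption. A formula-arm risk of 0.45 instead of 0.533 would bring one of the two confirmatory comparisons to about even odds at 30 per group, and to about two in three at 38. These figures assume that the plant-based risk is 0.176 as planned. They show sensitivity and do not predict the formula arm's risk.

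**What to change.** No change in N is needed. In the sample-size section:

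- Name the unpooled Z formula as the source of 30 per group.
- State the power of the adjusted logistic analysis: about 75–79% at 30 evaluable, and about 86–87% at 38 per arm with complete outcomes.
- Limit the 80% claim to plant-based versus conventional diet.
- Report power for plant-based versus formula separately, over a stated range of formula-arm risks, with the reason for the range.

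In the statistical methods or the SAP, specify the likelihood-ratio test, not the Wald test, for the confirmatory treatment effect.

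The cost is one paragraph and a line of SAP wording. The downside is that a stated figure becomes slightly less favourable and the weaker position of the formula comparison becomes visible.

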### Recruitment {20}

Participants will be recruited from two sites in Chengdu, China (West China Fourth Hospital, Sichuan University, and The Seventh People’s Hospital of Chengdu). Recruitment began on 10 January 2026. Potentially eligible patients will be identified through routine inpatient and outpatient oncology services and clinician referrals. Study information will be provided via clinic-based postings (posters/flyers) and the departments’ official online channels (e.g., website and WeChat public account). Interested patients will contact the study team by telephone or WeChat and will complete a brief pre-screening to assess key eligibility criteria, followed by on-site screening. Recruitment will be tracked using screening logs at both sites. If recruitment falls behind target, recruitment efforts will be intensified through clinician reminders, refreshed materials, expanded online dissemination, and adjustments to recruitment coverage and/or the recruitment period.

